### Overview of the Connected for Wellness Mobile App

In an effort to address the barriers to care for youth, a co-designed mobile app called Connected for Wellness was created with adolescents and their caregivers. The development of the Connected for Wellness mobile app and its predecessor, Connectd for Schools [26], is grounded in participatory informatics approaches. *Participatory informatics* [27] is an approach to technology codevelopment that combines best practices from community-partnered participatory research [28] and end user–centered participation in technology design [29]. This approach addresses community health priorities by including intended users as equitable partners throughout the design process. The codevelopment of the Connected for Wellness mobile app with youth and caregivers was led by the scientific team that includes diverse, multilingual research staff, child and adolescent psychiatrists, psychologists, technology development experts, and student researchers. The content includes engaging videos created by and representing diverse youth and caregivers in English and Spanish (details on the codevelopment process and protocols are reported elsewhere). In its final form, Connected for Wellness has four key components: (1) mental health and wellness education, (2) self-assessment tools, (3) emotion regulation and coping strategies, and (4) site-specific and community resources. The home page features a Get Help Now button that directly connects the user to 911 for those who need immediate assistance. The community resources include an embedded link to FindHelp, which is searchable by zip code. In addition to listings of financial assistance and free and reduced-cost food, housing, and health care, FindHelp also features helplines for specific needs such as domestic violence assistance and for communities that are particularly underserved. Given our priority to ensure that the app is widely accessible, we also developed a PDF document that provides all app content for anyone who is using a screen reader or prefers reading along.

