In addition, this study will explore how the app—co-designed with input from both youth and caregivers—enhances engagement with mental health support services and fosters help-seeking behaviors among youth and their families. Our main hypothesis is that the Connected for Wellness app will improve cascade-of-care outcomes compared to usual care. Specifically, we expect that youth at sites implementing the intervention will seek help more often, be screened more frequently, and be more likely to attend at least 3 mental health sessions if identified as needing services. If effective, the app has the potential to be a scalable tool for supporting youth mental health in community-based settings such as schools and primary care clinics and advancing public health approaches to connecting youth with care.

**Table 1 table1:** Features of the Connected for Wellness mobile app for youth and caregivers.

Feature (English and Spanish)	Description	Examples
Pathways [figure not shown]	Brief videos and quick tips on well-being topics	Getting better sleep Improving communication Grief and loss Social connectedness Relaxation Managing emotions Academic stress Mental health help seeking
Self-assessments [figure not shown]	Short questionnaires to gauge sleep and well-being (for youth and caregivers) and social determinant of health needs (for caregivers)	WHO-5^a^ PROMIS^b^ sleep items Social determinant of health questions
Directory [figure not shown]	Site-specific, local, and national resources with direct dial, maps, and information about resources	Hotlines Helplines Clinic- or school-specific mental health and social resources located on-site Community resources (FindHelp)
Toolbox [figure not shown]	Over 500 well-being activities and suggestions that can be saved in the “Toolbox”	Brief suggestions based on well-being frameworks that include domains of physical, psychological, emotional, spiritual, relational, professional, and cultural well-being

^a^WHO-5: World Health Organization–Five Well-Being Index.

^b^PROMIS: Patient-Reported Outcomes Measurement Information System.

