### Primary Outcomes: Cascade-of-Care Framework

The primary study outcomes are based on the cascade-of-care framework that focuses on population-level health needs and tracks individuals across relevant stages of a health care continuum [37,38]. Originally developed by the Juvenile Justice–Translational Research on Interventions for Adolescents in the Legal System [39,40], the steps in the cascade of care are identification of a behavioral health need, referral to behavioral health care, initiation of services, and engagement with services (>3 visits). The cascade of care has been adapted for youth in foster care [41]; this version was used for this study. Data on each step of the cascade of care will be obtained from deidentified electronic medical records and administrative data at the individual youth level from each of the study sites. This approach, which uses established databases, will enable comparison of cascade-of-care outcomes after implementation to data that were collected before preimplementation years. As detailed in the analytic plan in the Data Analysis section, individual-level data will be aggregated to the site level to test the hypothesis that implementation of the Connected for Wellness mobile app intervention is associated with improvements in youth progression through the cascade of care compared to the (preintervention) control condition. Improvements in the cascade of care are an established public health outcome as they help identify gaps in care and assess the effectiveness of the mobile app intervention. At a population level, in schools or primary care clinics, examining the cascade can inform how well an intervention improves youth access, engagement, and outcomes for a specific population and whether the intervention effectively addresses their unique needs and disparities. Statistical power was determined relative to the current level of each of the cascade outcomes (identification of mental health need, match to services, and initiation of services) in the sites as reflected in administrative data. Power was calculated separately for each cascade outcome. With a power of 0.8, an α value of .05, and 2-tailed tests, the planned design and sample sizes enable detection of small differences between the intervention and control conditions in all the cascade outcomes (2%-10%). Table 2 shows the operational definitions for the cascade-of-care outcome variables, and Table 3 shows the definitions, data collection, and outcomes.

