**Table 2 table2:** Cascade-of-care model based on Connected for Wellness triage outcomes.

Step	Rate	Operational definition
Youth at site (step a)	(a)	Total number of youth enrolled at a high school campus or on a patient panel at the primary care clinic site
Need identified (step b)	(b/a)	Subset of total enrolled youth (step a) who complete mental health and social determinant of health needs identification at school or the primary care clinic
Matched to services (step c)	(c/b)	Subset of youth with needs (step b) who receive a referral
Initiated services (step d)	(d/c)	Subset of those referred to services (step c) who initiate services (eg, first treatment session)
Engaged in services (step e)	(e/d)	Subset of those who initiate services (step d) who have ongoing sessions (≥3 visits)

**Table 3 table3:** Primary outcomes based on the cascade-of-care framework and covariates for generalized linear mixed model (GLMM) analysis.

Cascade step	Operational definition and data description	Covariates in GLMM
Need identified	Youth who completed self-assessments or were flagged by navigators	Age, gender, race, ethnicity, site type (school vs clinic), and urban or rural
Matched to services	Referral documented in site records or follow-up logs	All the aforementioned covariates+previous mental health history if available
Initiated services	Attended first mental health appointment	Same as the previous covariates
Engaged in services	≥3 treatment sessions attended	Same as the previous covariates+time since app onboarding

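### The primary outcome 'need identified' counts completed assessments rather than needs, serves as the referral denominator, and is contradictory on whether app self-assessments count

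*Protocol article*

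**What the plan says.** Two tables in the section on primary outcomes define step b of the cascade, need identified.

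- Table 2 takes the enrolled youth "who complete mental health and social determinant of health needs identification at school or the primary care clinic" and reports them as a proportion of all youth at the site (b/a).
- Table 3 gives the same step as "Youth who completed self-assessments or were flagged by navigators".
- Step c in Table 2 is "Subset of youth with needs (step b) who receive a referral", reported as c/b. Step b is thus both the numerator of one primary outcome and the denominator of the next.

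On where the data come from, the text above the tables states: "Data on each step of the cascade of care will be obtained from deidentified electronic medical records and administrative data". Yet the caption of Table 2 reads "Cascade-of-care model based on Connected for Wellness triage outcomes". In Table 1, Self-assessments is a named app feature, described as "Short questionnaires to gauge sleep and well-being (for youth and caregivers) and social determinant of health needs (for caregivers").

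**The concern.** There are two linked problems.

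First, completing an assessment is not the same as having a need. The app overview says that WHO-5 users are classed as low, moderate or high in well-being. A youth who completes an assessment and does well still meets the wording of step b, and then sits in the denominator of the referral rate as someone with a need. The Data Analysis section itself separates being screened from being identified as needing services. It also hypothesises more frequent screening and improvement in all cascade outcomes. Under the stated definition, extra screening pushes two of those outcomes in opposite directions.

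Second, the tables and text disagree on whether app self-assessments count. All clusters begin without the app, so if they did count, one route into step b would be open only under intervention. The intervention contrast on b/a would then partly measure how the outcome is ascertained.

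At stake is what a rise in b/a, or a fall in c/b, could be taken to mean.

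**Working it through.** **Text comparison**

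| Question | Points to app self-assessments counting | Points to site records only |
|---|---|---|
| What does 'self-assessment' mean? | Outside Table 3, the term is used only for app tools (app overview, Table 1) | Table 3 does not say in-app |
| What is the source? | Caption of Table 2 refers to the app's triage outcomes; the step b row of Table 3 names no source, while the step c row names site records or follow-up logs | The outcome section draws every step from medical records and administrative data |
| Where is it completed? | – | Table 2: at the school or clinic |
| Can app data be linked to a youth's record? | – | Users enter no identifiers (consent section) and remain anonymous (Ethical Considerations) |
| Does the outcome exist under control? | The app does not (Stepped-Wedge Design) | A current level is said to exist in administrative data; navigators were already in place (Setting and Participants) |

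On the separate question of a positive result, both tables agree: neither requires one. That finding does not depend on the source.

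**The plan's own figure.** The article says differences of 2%-10% are detectable. This cannot be reproduced from the article, which gives no number of youth, baseline rates or intracluster correlation. It is used below only for scale, read as percentage points, which the article does not state.

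**Illustration.** All inputs are assumptions:

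- p0 = control b/a
- r = control c/b
- s = share of youth not already in step b who complete an assessment under intervention, without any of them having a newly identified need or a referral

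Referrals stay at r × p0 of all youth. Then:

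- new b/a = p0 + s(1 − p0)
- new c/b = r × p0 / [p0 + s(1 − p0)]

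With p0 = 10%, r = 50%, s = 10%:

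- b/a = 0.10 + 0.10 × 0.90 = 0.190, a rise of 9.0 points
- c/b = 0.05 / 0.190 = 0.263, a fall of 23.7 points
- check: c/a = 0.190 × 0.263 = 0.05, unchanged

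With s = 5%:

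- b/a = 0.10 + 0.05 × 0.90 = 0.145, a rise of 4.5 points
- c/b = 0.05 / 0.145 = 0.345, a fall of 15.5 points

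Range over the assumed baseline, with r = 50% and s = 10%:

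| p0 | new b/a | change in b/a (points) | new c/b |
|---|---|---|---|
| 5% | 14.5% | +9.5 | 17.2% |
| 10% | 19.0% | +9.0 | 26.3% |
| 20% | 28.0% | +8.0 | 35.7% |
| 30% | 37.0% | +7.0 | 40.5% |

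The completion share that produces a spurious rise of d is s = d/(1 − p0). For p0 from 5% to 30%:

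- d = 2 points: 0.02/0.95 = 2.1% to 0.02/0.70 = 2.9%
- d = 10 points: 0.10/0.95 = 10.5% to 0.10/0.70 = 14.3%

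Modest extra completion would therefore cover the stated detectable range. The formula holds whatever the source of the extra completions. If app completions are excluded, their contribution to s is zero, and only extra screening in site records remains.

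Of the later steps, only c/b is affected directly, because d/c and e/d have c and d as denominators.

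**The case against.** The strongest reply is that app self-assessments never enter the outcome. The article names site records as the source for every step, makes app use anonymous with no stated link to those records, and places completion at the school or clinic. Table 2 also asks for mental health and social-determinant identification, while Table 1 gives the app's social-determinant questions to caregivers only. On that reading a youth's in-app WHO-5 would not satisfy step b at all. Navigators predate the app, and a control level of the outcome is said to exist.

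This reply stands against one stronger inference. A reader might conclude that b/a rises by construction because the control condition has no app. The documents do not establish that, because they contradict themselves on whether app completions count. If only site records count, the app artefact is zero.

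A second reply is that more screening is a declared aim, so a rise in completion is partly an intended effect. That is fair, and it would be too much to say that b/a measures nothing but app delivery. It does not justify labelling completion as need or using completers as the denominator for referral.

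Neither reply removes the definitional fault. If app completions are excluded, the wording of Table 3 still has to change.

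**Conclusion.** The point holds in two parts of different strength.

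- **Firm on any reading.** Both tables let a completed assessment qualify as an identified need without a positive result, and Table 2 then uses that group as the denominator of c/b. Extra screening alone would raise b/a and lower c/b.
- **Conditional.** If in-app self-assessments were counted, ascertainment would differ between conditions. With an assumed 10% control b/a and 50% c/b, completion by 10% of the remaining youth would give 19.0% and 26.3% with no true effect. If they are not counted, this added artefact is zero.

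The sizes are illustrative, since the article reports neither baseline rates nor app uptake, and they assume that the extra completers bring no additional need or referral. A proven bias should not be inferred. What is shown is a primary outcome whose meaning is wrong as written and whose source is contradictory.

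**What to change.** Before data extraction:

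1. Define step b identically in Tables 2 and 3 as an identified mental health need (a positive screen, a documented need or a navigator flag), taken from the same site-record source in both conditions.
2. State that in-app self-assessments do not count towards the primary outcome, and align Table 3 and the caption of Table 2 with the stated source and the anonymity of app use.
3. Report screening completion and in-app WHO-5 completion separately, so that the screening hypothesis keeps its own measure.
4. Reconcile the social-determinant wording of Table 2 with Table 1, where that questionnaire is "social determinant of health needs (for caregivers") only. Dropping it from step b is one option, but that is the investigators' choice.

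The wording change is cheap. The expected effect on b/a becomes smaller. Sites must also confirm that their records hold screen results, documented needs or navigator flags in both periods, which the article does not show.

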### Ethical Considerations

This study has been reviewed and approved by the IRB at the University of California, Riverside (protocol 30090). All study procedures involving human participants adhere to institutional and national ethical standards. Informed consent is obtained via the app using both video and text formats. Participants complete comprehension questions to ensure understanding. Only youth who correctly answer the questions and indicate consent may proceed. Parental consent is required for youth aged <18 years and per institutional policy. No personally identifying information is collected. Data are fully anonymized, and site-level dashboards track aggregate use only. App use is voluntary, and users remain anonymous throughout. Participants are not compensated for using the app, which is designed as a universal public health intervention. Site staff (peer ambassadors and navigators) may receive stipends through partner institutions. No images or materials in this study contain identifiable participant information.

### Data Monitoring Plan

A data safety monitoring board (DSMB) will oversee the study to ensure participant safety, data integrity, and protocol adherence. The DSMB will review cumulative data at scheduled intervals and advise on any modifications needed to protect participants. The study team will conduct routine internal data quality checks, with any protocol deviations or serious concerns reported promptly to the DSMB and IRB.

### Data Management Plan

Study data will be collected using HIPAA (Health Insurance Portability and Accountability Act)-compliant, encrypted platforms, with all records linked to unique participant IDs to ensure confidentiality. Data will be stored on secure, password-protected institutional servers with regular backups. Data management procedures—including entry, coding, cleaning, and storage—will follow standard operating procedures and be documented for transparency and reproducibility.

### Plan for Collection and Reporting of Harms

All adverse events will be systematically recorded and reported per IRB and National Institutes of Health guidelines. Study personnel will be trained to monitor and respond to participant distress or risk disclosures, with serious adverse events reported to the DSMB and IRB within 48 hours. The DSMB will review all safety reports and provide recommendations for continuation or modification of study procedures as needed.

### Data Access and Use

Access to identifiable data will be limited to authorized study staff approved by the IRB. All data use will comply with established data use agreements with the participating schools and clinics.

### Dissemination Plan

All dissemination materials—including publications, presentations, and community reports—will be reviewed to ensure participant confidentiality and adherence to ethical standards. Community-facing materials will be developed in accessible formats and, when appropriate, cocreated with community partners.

### Data Analysis

Analyses will be conducted using the SAS statistical software (version 9.4; SAS Institute) [42]. Preliminary analyses will include examination of descriptive statistics, distributions, and internal consistency reliability of scaled measures. The primary hypotheses are that the Connected for Wellness mobile app will improve all cascade outcomes relative to the usual care control condition. Specifically, we hypothesize that the mobile app will affect site-level increases in the progression through the defined cascade of care, as defined in Table 2 (eg, youth at sites implementing the Connected for Wellness mobile app intervention will engage in more help seeking and be screened more frequently, and once screened and identified as needing mental health services, youth will be more likely to attend at least 3 sessions as compared to the control conditions [before implementation of the mobile app intervention]).

These hypotheses will be tested within a generalized linear mixed model (GLMM) framework implemented using the SAS PROC GLIMMIX statement. These models accommodate variously distributed dependent variables, including dichotomous outcomes such as those reflecting the cascade-of-care outcomes, and account for correlations among measurements of the same participants and nesting of youth within sites. Models will use a binomial distribution and a logit link function. All tests will be 2-tailed with a significance level of *P*=.05. For dichotomous outcomes, we will use a binomial distribution with a logit link function.

The GLMM models will include county and intervention (vs control) as fixed effects, with site and youth as random effects. Study month will be treated as a continuous variable to account for potential secular trends. The primary focus will be on the intervention effect. For youth with mental health need, we will also examine time-to-event outcomes (eg, days to service initiation) using Poisson models with a log link function. If overdispersion is detected, we will use a negative binomial model. The relative risk ratio for intervention will indicate whether the app reduces time to service matching and initiation. To address heterogeneity, the GLMM will include random intercepts for sites and fixed effects for county and wave. We will test for interactions between intervention status and site characteristics (eg, urban vs rural and school vs clinic). We will also conduct stratified analyses by key demographic variables (race and ethnicity, age, and gender) to explore subgroup effects.

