In addition, the app uses a peer-based (*user-user*) approach, which identifies users with similar engagement patterns and recommends resources that those similar users have found helpful but the current user has not yet accessed. A second layer of intelligence involves user classification, where youth responses to in-app wellness screeners trigger tailored protocols and personalized content recommendations based on their identified needs. Specifically, Connected for Wellness includes the World Health Organization–Five Well-Being Index (WHO-5) [30], a short questionnaire that measures a person’s well-being over the previous 2 weeks and is suitable for children aged ≥9 years. Users can access this questionnaire on their own and will be reminded to complete it monthly through a notification. Higher scores on the WHO-5 indicate better mental well-being, whereas lower scores indicate potential risk of mental health concerns. After responding to the well-being questions, users receive a well-being score categorized as low, moderate, or high. On the basis of their score, they are provided with personalized well-being activities and suggestions, which can be saved in the app’s Toolbox section for easy access later. For example, a user who scores low on the WHO-5 will receive recommendations for professional help seeking, along with evidence-based strategies to support well-being, such as behavioral activation and emotion regulation techniques. Figure 1 illustrates how the WHO-5 normed scoring system guides the Toolbox recommendations and suggestions for help seeking provided to users based on their check-in results (ie, scores on the WHO-5: green** **for high well-being,** **yellow for moderate well-being, and orange for low well-being).

The primary objective of this study is to evaluate the effectiveness of the Connected for Wellness mobile app in enhancing youth engagement with mental health services when implemented in schools and primary care settings. This study aims to leverage the app’s ability to deliver evidence-based, culturally and contextually relevant information to address key barriers to mental health care, including stigma, limited accessibility, and the need for youth autonomy and confidentiality.

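### The engagement hypothesis concerns ≥3 sessions among youth with identified need (e/b), but Table 2 defines engagement among youth who have already started services (e/d)

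*Protocol article*

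**What the plan says.** The engagement outcome is described in four places in the protocol article.

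- **Introduction, main hypothesis** (end of the app overview, before Table 1): youth at intervention sites will "be more likely to attend at least 3 mental health sessions if identified as needing services".
- **Data Analysis**: the general statement is "The primary hypotheses are that the Connected for Wellness mobile app will improve all cascade outcomes relative to the usual care control condition". The next sentence speaks of "site-level increases in the progression through the defined cascade of care, as defined in Table 2", and then gives, in a parenthesis introduced as an example, "once screened and identified as needing mental health services, youth will be more likely to attend at least 3 sessions".
- **Table 2**: engagement (step e) has the rate e/d and is defined as "Subset of those who initiate services (step d) who have ongoing sessions (≥3 visits").
- **Table 3**: the engagement row says only "≥3 treatment sessions attended" and gives no denominator.

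The section on primary outcomes presents Table 2 as the operational definition of the cascade variables. Each Table 2 rate is conditional on the step before it: b/a, c/b, d/c, e/d. No row has the rate e/b.

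**The concern.** The two hypothesis statements start from youth found to need services, and Table 2 starts from youth who have attended a first session. These are different estimands. The first asks whether a young person with identified need ends up with at least 3 sessions. The second asks whether a young person who has started care stays in it.

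The gap between them consists of referral and initiation, two steps that the primary hypotheses expect the app to improve. If it does, the group in the e/d denominator changes with rollout. Initiators before and after may then differ in need or motivation, and e/d compares differently selected groups.

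At stake is the conclusion on one of the four primary outcomes. With both wordings in the protocol, a result could be reported as confirming or not confirming the engagement hypothesis according to which denominator is taken up once the data are known.

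**Working it through.** **1. The plan's own figure.** The power statement reads "With a power of 0.8, an α value of .05, and 2-tailed tests" and claims that differences of 2% to 10% are detectable. The article gives no baseline rates, youth counts or intracluster correlation, so this cannot be reproduced. Its bracketed list of outcomes names need, match and initiation but not engagement, so it does not show which engagement denominator was meant.

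**2. The denominators side by side.**

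| Place | Denominator for ≥3 sessions | Rate |
|---|---|---|
| Introduction, main hypothesis | identified as needing services | e/b |
| Data Analysis, example in parenthesis | screened and identified as needing services | e/b |
| Table 2, step e | initiated services | e/d |
| Table 3, engagement row | not stated | – |

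Equating identified need with step b follows Table 2's own label for that step and its row for step c, which treats step b as the youth with needs.

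**3. The identity.** For any counts, e/b = (c/b) × (d/c) × (e/d). The relative change in e/b equals that in e/d only if the product (c/b)(d/c) is unchanged.

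**4. Illustration.** All counts are assumed. The p values come from pooled two-proportion z tests that ignore clustering and secular trend; they are not the planned mixed model.

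| Case | b | c | d | e | c/b | d/c | e/d | e/b |
|---|---|---|---|---|---|---|---|---|
| Control | 1000 | 500 | 250 | 150 | 50% | 50% | 60% | 15.0% |
| App, A | 1000 | 600 | 360 | 216 | 60% | 60% | 60% | 21.6% |
| App, B | 1000 | 600 | 360 | 198 | 60% | 60% | 55% | 19.8% |
| App, C | 1000 | 650 | 420 | 210 | 65% | 64.6% | 50% | 21.0% |
| App, D | 1500 | 600 | 270 | 189 | 40% | 45% | 70% | 12.6% |

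- **A:** e/b rises 6.6 points (z = 3.82, p = 0.0001); e/d does not move.
- **B:** e/b rises 4.8 points (z = 2.83, p = 0.005); e/d falls 5 points (z = −1.23, p = 0.22).
- **C:** for e/b, the pooled rate is 360/2000 = 0.18, SE = √(0.18 × 0.82 × 2/1000) = 0.0172, z = 0.06/0.0172 = 3.49, p = 0.0005. For e/d, the pooled rate is 360/670 = 0.537, SE = √(0.537 × 0.463 × (1/250 + 1/420)) = 0.0398, z = −0.10/0.0398 = −2.51, p = 0.012. The two rates move in opposite directions, each with p < 0.05.
- **D:** e/d rises 10 points (p = 0.017) while e/b falls 2.4 points (p = 0.09).

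**5. Break-even.** If c/b and d/c both go from 50% to 60%, e/b improves unless e/d drops below 0.15/(0.6 × 0.6) = 41.7%, from 60%.

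**6. Why e/b is not sufficient either.** In case D identification widens from 1000 to 1500. If enrolment a is the same in both conditions, youth with ≥3 sessions rise from 150 to 189, so e/a goes up by a factor of 189/150 = 1.26 although e/b falls. Step b is itself an outcome that the app may change.

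**The case against.** The strongest reply is that the article ranks its own texts. Table 2 is called the operational definition, the Data Analysis sentence refers to it, and the need-based wording there is only an example. On that view e/d is intended and the prose is loose. This stands in part: it would be wrong to say that the article gives no guidance on which definition governs. But an example should be an instance of what it illustrates, and e/b is not a Table 2 rate. The wording also appears in the Introduction without being marked as an example. The Data Analysis section uses a need-based group again for days to service initiation. If e/d is meant, both hypothesis statements are wrong as written and still need correcting.

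Four stronger readings are tempting, and the document does not support them.

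- *The trial would miss the app's effect on access.* It would not: c/b and d/c are primary outcomes. In case A both would show the gain, and a flat e/d would correctly describe retention.
- *Hypothesis and table share only the screening rate.* This treats examples as a full list. Both hypothesis statements open with improvement in the cascade outcomes generally.
- *Step e is the outcome named in the primary objective.* The objective, "enhancing youth engagement with mental health services when implemented in schools and primary care settings", uses engagement in a general sense and does not cite step e.
- *The trial's data will give contradictory answers.* They can, but how likely this is depends wholly on assumed rates. Case D also has the app lowering referral and initiation rates, which nothing in the article suggests.

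**Conclusion.** The inconsistency is real and lies in the denominator of a primary outcome. The hypothesis as stated twice is about e/b; the operational table it relies on gives e/d. Testing e/d alone therefore does not test that hypothesis, and it does so in a group selected by initiation, which the app is expected to affect.

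The algebra holds whatever the rates. How large the divergence would be in this trial cannot be derived from the article: the shifts shown, from no change in e/d against +6.6 points in e/b up to opposite directions, are illustrations from assumed counts without clustering or time trend. The consequence is limited to the engagement conclusion, since referral and initiation have their own primary rates. It should be corrected before analysis, and the correction is small.

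**What to change.** Before analysis, name one denominator for the primary engagement test and use it in the Introduction hypothesis, the Data Analysis section, Table 2 and Table 3. Either route is acceptable:

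1. Add e/b (≥3 sessions among youth with identified need) as the test of the hypothesis as worded, and keep e/d as the step rate that shows where a gain or loss arises.
2. Reword both hypothesis statements to e/d, so that Table 2 stands unchanged, and report e/b as a prespecified overall measure.

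In both cases state the denominator in Table 3's engagement row and report e/a alongside, because step b can change with the app. Help seeking appears in both hypothesis statements but has no step in Table 2; tie it to the cascade step that measures it or drop it from the hypothesis.

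The cost is a few sentences, table edits, and one or two additional models on counts already collected for steps a to e. The Results section reports that no hypothesis results exist yet, so the choice can still be made without knowledge of the data.
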